There are over 70 frailty assessments aimed at identifying or measuring the extent of frailty, many of which are multidimensional and include assessments of physical and cognitive function, nutritional status, comorbidities, and other factors that might affect the patient’s physiologic reserve or tolerance for surgery (13, 15). Clinicians’ impressions of frailty *via* bedside assessments have also demonstrated strong predictive capacity for identifying patients at risk of significant surgical morbidity or mortality (16). One strategy to manage surgical risk following identification of vulnerability is prehabilitation. Prehabilitation refers to assessments and interventions initiated prior to treatment to create physiologic and psychosocial buffers that can be protective against anticipated deconditioning, complications, and chronic morbidity that occur as a result of the treatment itself (17, 18). Contemporary prehabilitation is multimodal, often including a combination of exercise, enhanced nutrition, stress management, smoking cessation, and medical optimization strategies—strategies that are also commonly used to reduce frailty.

Systematic reviews and meta-analyses of prehabilitation prior to cancer surgery have reported encouraging findings, including improved physical fitness, length of stay, surgical complication rates, and HRQOL (19–24). In recent years, growing attention has been paid to patients who are frail, higher risk, and/or vulnerable to surgical complications, and thus likely to benefit most (25–27). For example, Barberan-Garcia et al. (26) conducted an RCT of prehabilitation in 174 ‘high-risk’ patients defined as older than 70 years and/or an American Society of Anesthesiologists score of III/IV, over half of whom were oncology patients. The intervention was feasible and safe, and prehabilitation reduced postoperative complications by half compared to the control group. Importantly, in a follow-up economic analysis, their intervention cost 389 Euro and yielded a six-fold reduction in risk of hospital readmissions at 30 days, collectively yielding a potential cost savings of up to approximately 800 Euro per patient (28). Aligned with these emerging data are implementation recommendations that include triaging strategies that prioritize prehabilitation for ‘at-risk’ or ‘frail’ patients for whom the benefits and cost effectiveness are likely to be greatest (29–31).

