Reporting of the exercise prescription parameters and adherence to the programming will follow the Consensus on Exercise Reporting Template (62). Adherence to home and facility-based exercise sessions are recorded *via* attendance and standardized logbooks capturing training activity completed by the research coordinator. Adherence to stress management, nutrition plan, protein consumption, and utilization of smoking cessation tools (as required) is recorded weekly using a logbook within the participant manuals. Healthy eating practices advised by the dietitian are also assessed by a 3-day diet record in the week prior to surgery. Safety or adverse events related to prehabilitation are discussed during weekly communication between the participants and the research coordinator. Reporting and grading of adverse events will follow the Common Terminology Criteria for Adverse Events version 5.0 (63).

Estimates of program effectiveness are derived from a combination of patient-reported and functional performance measures, as well as clinical information from the medical record at each of the study timepoints. Aerobic functional capacity is measured using the Six-Minute Walk Test (6MWT) (64) and musculoskeletal functional capacity is assessed *via* grip strength using an isometric dynamometry (Jamar, Sammons Preston, Bolingbrook, IL, U.S.A.) according to established protocols (44). Body mass (kilograms) and height (meters) are measured using standardized procedures and are used to calculate body mass index (BMI, kg/m^2^). Body fat percentage, fat and fat free mass, impedance, resistance, and phase angle are recorded are measured *via* bioelectrical impedance analysis (mBCA 514, Seca, Hamburg, Germany) (65). HRQOL is measured using the 12-item Short Form Health Survey (SF-12) (66, 67) and the EuroQol 5 Dimensions 5 Levels (EQ5D-5L) (68) The Patient Health Questionnaire (PHQ-9) is used to assess depression (69). The EFS, PSS, and GLTEQ are also re-administered at each follow-up timepoint. Postoperative length of stay in number of days (including any readmissions) is recorded from the medical record. Complications, including mortality, are reported according to the Clavien-Dindo classification (70). All health events that require readmission will also be documented. Complication and health event data are extracted from the medical record at the 30^th^ and 90^th^ postoperative day for each participant.

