Economic evaluation will be conducted from the perspectives of the individual and the hospital. Cost for an individual prehabilitation participant will be calculated on two fundamental components: the quantity of resources consumed and the unit cost of those resources related to prehabilitation. The EQ5D-5L will be used for the cost–effectiveness analysis as the health effect to determine the quality-adjusted life years (QALY) for the 90-day follow-up time period. The calculated participant costing and QALY will be used to determine the incremental cost–effective ratio (ICER). ICER will be calculated as a ratio of the difference in patient costing and the difference in QALY between FBP and HBP [ICER = (cost_FBP_ – cost_HBP_)_/_(QALY_FBP_ – QALY_HBP_)]. This will be calculated for both the program (measured cost for delivery of FBP and HBP) and patient perspective. Patient-perspective costing is measured by a patient-reported cost-diary that includes: direct healthcare cost (impact of the interventions on the use of healthcare services, such as visits to the general practice, specialist care, prescribed medication); direct non-healthcare costs (cost incurred by the patient and the family, such as cost of over-the-counter medication, cost of health activities, hours of paid and unpaid household help, transportation, and value of other out-of-pocket expenses, with specifics on exercise-related expenses); and indirect costs (value of productivity lost due to illness-related absence, including number of days absent from work, days lost from housekeeping, and other daily activities). A cost–impact from the perspective of the hospital will be conducted based on surgery-related hospital length of stay, readmission frequency, and length of stay of readmission(s) will be used to determine cost differences between those that participate in prehabilitation versus usual care participants. Cost impact will be estimated by applying the unit cost of an inpatient hospital day to the differences for participants that enrolled in prehabilitation and those that did not. Data from the Canadian Institute for Health Information on average cost of hospital stay will be used for the respective year.

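### The hospital cost comparison with usual care omits the cost of delivering the programme, so it yields a gross inpatient offset and not a net saving

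*Protocol article*

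**What the plan says.** The economic evaluation, under Study Outcomes in the Protocol article, takes the perspectives of the individual and the hospital and contains two comparisons.

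- **Facility-based (FBP) against home-based (HBP) prehabilitation.** This is the incremental cost-effectiveness ratio (ICER): "ICER will be calculated as a ratio of the difference in patient costing and the difference in QALY between FBP and HBP". On the perspectives it adds: "This will be calculated for both the program (measured cost for delivery of FBP and HBP) and patient perspective". The printed formula has FBP and HBP terms only.
- **Prehabilitation against usual care.** This is the hospital cost-impact. Its inputs are given as "surgery-related hospital length of stay, readmission frequency, and length of stay of readmission(s) will be used to determine cost differences", and its pricing rule is "Cost impact will be estimated by applying the unit cost of an inpatient hospital day to the differences for participants that enrolled in prehabilitation" as against those who did not enrol. On the source of the unit cost: "Data from the Canadian Institute for Health Information on average cost of hospital stay will be used for the respective year".

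Earlier in the same section, among the clinical outcomes, the length-of-stay variable is defined: "Postoperative length of stay in number of days (including any readmissions) is recorded from the medical record".

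RQ1j in Box 1 asks about both the costs of prehabilitation and the savings it may bring. It is one of the feasibility questions, and feasibility is the primary objective.

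**The concern.** A hospital that sets up this service pays for staff and materials and hopes to recover the money through shorter stays and fewer readmissions. The hospital-perspective result against usual care has to hold both sides of that account. As described, it holds only the recovery side.

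Under Sample Size, usual-care participants are described as making their hospital records available. The cost-impact is thus the only economic comparison described that involves them. If delivery cost is missing there, no described analysis sets the cost of the service against what it saves.

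The Prehabilitation Program section shows that delivery uses real resources: supervised facility sessions, weekly calls from a kinesiologist, dietitian and psychologist consultations, and free equipment and protein. A gross figure reported in answer to RQ1j could make a service that costs the hospital money look as if it saves money.

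A smaller matter lies in the length-of-stay terms. One part of the section defines a stay that includes readmissions. Another lists readmission stay as a separate input. An analyst could combine the two wrongly.

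**Working it through.** The article states no cost, saving, stay difference or day cost for this trial, so there is no figure to reproduce. The check is algebraic, followed by an illustration on assumed values.

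**Notation, per patient**
- dI = difference in index-stay days, usual care minus prehabilitation
- dR = difference in readmission days, same direction
- u = cost of one inpatient day (external source, no figure given)
- c = programme delivery cost per prehabilitation participant (measured under the plan, no figure given)

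**Step 1: the rule as written.** The inputs are inpatient items and the multiplier is the day cost. With each day counted once, the saving is u(dI + dR). There is no c.

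**Step 2: the net hospital result.** The hospital also bears c for each prehabilitation participant, so the net saving is u(dI + dR) − c.

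**Step 3: the gap.** u(dI + dR) − [u(dI + dR) − c] = c. The gap equals the delivery cost whatever the stay results are, and always favours prehabilitation. A positive gross saving becomes a net loss when c exceeds u(dI + dR).

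**Step 4: illustration.** All values are assumed and expressed in units of one inpatient-day cost (u = 1).
- dI = 1.0, dR = 0.5: gross saving 1.0 + 0.5 = 1.50. With c = 0.25, 0.5 and 1.0 the net saving is 1.25, 1.00 and 0.50.
- dI = 0.5, dR = 0.25: gross saving 0.5 + 0.25 = 0.75. With c = 0.25, 0.5 and 1.0 the net result is 0.50, 0.25 and −0.25. The last is a net loss that the rule as written would show as a saving.

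**Step 5: the length-of-stay terms.** Two readings of the cost-impact are possible.
- The surgery-related stay is the index admission, and readmission stay is added. The result is u(dI + dR), each day counted once.
- The first term is the recorded postoperative stay, which already contains readmissions, and readmission stay is added to it. The result is u(dI + 2dR).

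Under the second reading the saving changes by the factor (dI + 2dR)/(dI + dR). On assumed values:
- For dI from 0.5 to 2.0 and dR from 0.25 to 1.0, the factor runs from 2.50/2.25 = 1.11 (dI = 2.0, dR = 0.25) to 2.50/1.50 = 1.67 (dI = 0.5, dR = 1.0).
- With dR = 0 it is 1.00.
- With dR = −0.25 it runs from 0.00/0.25 = 0.00 (dI = 0.5) to 1.50/1.75 = 0.86 (dI = 2.0), so the saving would be understated.

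The direction follows the sign of dR. The effect arises only under the second reading.

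**The case against.** The strongest defence is that delivery cost is not left out of the evaluation as a whole. The plan costs each participant's resources and measures delivery of both programme forms. RQ1j asks for costs as well as savings, and a reader given both could subtract one from the other. The article never calls the cost-impact a net saving. The trial is a pilot with no decision rule resting on this figure, its Discussion already limits what comparisons with usual care can bear, and an article may condense fuller costing detail.

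Part of this stands. The plan is not blind to delivery cost, and the result would mislead only if the gross figure were presented as the saving. But the article does not merely stay silent. It gives the inputs, the multiplier, the source of the unit cost and the groups compared, and delivery cost is not among them. It assigns that cost to a different comparison. Subtraction by the reader would also give no confidence interval for the net figure, although the Analytic Plan puts its emphasis on intervals.

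Two stronger readings are tempting and are not supported.

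- **That the plan counts readmission days twice.** The cost-impact names surgery-related stay apart from readmission stay, which reads naturally as index stay plus readmission stay. Nothing says that the combined variable is its first term, or that the listed items are simply summed. Double counting is a risk created by two descriptions, not a stated rule.
- **That the Introduction's figures size the problem.** The economic analysis of another trial is cited there, where "their intervention cost 389 Euro" and the potential saving was up to about 800 Euro. Those figures are not inputs to this plan. The article does not make clear whether the saving is before or after the programme cost, and neither figure describes this programme or this hospital.

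**Conclusion.** The concern holds for delivery cost. As written, the hospital comparison with usual care is a gross inpatient offset. It exceeds the net hospital saving by exactly the delivery cost per prehabilitation participant and so does not by itself answer the savings part of RQ1j. This follows from the stated rule and needs no assumption about the stay results. It does assume that the hospital bears the delivery cost, in line with the hospital perspective and with delivery cost being treated as a programme cost.

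The size in money is unknown, because it depends on trial data that the article does not give. The illustration shows only that the sign can change when delivery cost exceeds the inpatient offset.

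On length of stay, the supported conclusion is narrower: two descriptions need to be reconciled. Double counting is not established.

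The point should be settled before analysis. It does not undermine the rest of the feasibility assessment.

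**What to change.** 1. State that the hospital-perspective result against usual care is net: the inpatient cost difference (prehabilitation minus usual care) plus the measured delivery cost per prehabilitation participant, with a confidence interval.
2. Keep the inpatient-only figure if it is wanted, labelled as a gross inpatient offset.
3. Define the stay used for costing as index-admission days plus readmission days, each counted once, and say how this relates to the recorded postoperative stay that includes readmissions. Say also what part readmission frequency plays, since a per-day price already values readmissions through their days.

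This takes a few sentences of wording. Stay and readmissions come from the medical record, and delivery cost is already to be measured, so no new kind of data is needed; index and readmission days have only to be kept apart when they are extracted. The price is that the reported saving becomes less favourable to prehabilitation.

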### Analytic Plan

The analytic plan is described for prehabilitation implementation feasibility outcomes and exploratory analyses of prehabilitation effects. In line with comparative effectiveness research, presentation of confidence intervals will be emphasized for the purpose of accurately reflecting the actual data as well as directly addressing the uncertainty of the data. All quantitative analyses will be conducted in R (R Foundation for Statistical Computing, Vienna, Austria) and an alpha of.05 will be used.

Demographic and disease characteristics of all referred patients, as well as prehabilitation and usual care participants**’** will be summarized with appropriate parametric and non-parametric statistics. Reasons for ineligibility, declined participation in the study or intervention, as well as reasons for choosing FBP or HBP will be tallied. Group comparisons for referral information (surgical service, type of cancer, type of surgery, age, sex, and geographic location) will be assessed by one-way analysis of variance (ANOVA) for continuous and Chi-square test for categorical variables and described across FBP, HBP, usual care, and participants who decline participation. Baseline demographic and disease-related variables will be compared between study participants (FBP, HBP and usual care) ***via*** one-way ANOVA for continuous variables and Chi-square test for categorical variables.

Adherence to the interventions will be summarized dichotomously as meeting or not meeting the prescribed intervention components across each domain (exercise, nutrition, psychology, and smoking cessation). Reasons for deviations will be thematically categorized and summarized by frequency and percentage. Retention rates will be calculated as a total percentage of dropouts at the presurgical time point to the total participants enrolled for FBP and HBP. Reasons for dropout will be summarized using frequencies and percentage for each prehabilitation arm. Reported safety or adverse events will be summarized using frequencies and percentage for each group.

To provide an estimate of effect of HBP and FBP, point estimates and 95% confidence intervals will be calculated for changes in physical fitness, patient-reported outcomes from baseline to the 90-day time point using linear mixed effect models. Estimated mean hospital length of stay for HBP, FBP, and usual care, as well as between-group differences, will also be conducted using a linear mixed effect model. Incidence rate ratios and estimating rate differences for postoperative complication, readmission, and morbidity for prehabilitation in reference to usual care at 30 and 90 days after surgery will be made using Poisson regression. Tukey HSD will be used to adjust for multiple comparisons. In the presence of outliers, bootstrapping regression coefficient methodology will be done to obtain valid confidence intervals.

Semi-structured interviews regarding participant satisfaction as well as facilitators and barriers with the intervention will be transcribed verbatim and undergo qualitative content analysis. Initial transcript sample readings will be independently done by two researchers. Preliminary themes will be noted, and differences will be resolved, and duplications will be eliminated. Themes and content will be analyzed descriptively. Coding, linking, and retrieving the qualitative data will be conducted using NVivo software (QSR International, Melbourne, AUS).

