**Methods:**

This is a pilot pragmatic clinical trial conducted in a large academic hospital in Toronto, Ontario, Canada to assess feasibility of clinical implementation and derive estimates of effectiveness. Feasibility data include program referral rates, enrolment and attrition, intervention adherence and safety, participant satisfaction, and barriers and facilitators to programming. The study aims to receive 150 eligible referrals for adult, English-speaking, preoperative oncology patients with an identified indication for prehabilitation (*e.g*., frailty, deconditioning, malnutrition, psychological distress). Study participants undergo a baseline assessment and shared-decision making regarding the intervention setting: either facility-based prehabilitation or home-based prehabilitation. In both scenarios, participants receive an individualized exercise prescription, stress-reduction psychological support, nutrition counseling, and protein supplementation, and if appropriate, smoking cessation program referrals. Secondary objectives include estimating intervention effects at the week prior to surgery and 30 and 90 days postoperatively. Outcomes include surgical complications, postoperative length of stay, mortality, hospital readmissions, physical fitness, psychological well-being, and quality of life. Data from participants who decline the intervention but consent for research-related access to health records will serve as comparators. The COVID-19 pandemic required the introduction of a ‘virtual program’ using only telephone or internet-based communication for screening, assessments, or intervention was introduced.

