## Study Objectives

The primary objective of this study is to assess the feasibility of delivering a multimodal surgical prehabilitation service to surgical oncology patients. The secondary objectives are to explore the effectiveness of the program using clinical, physical, and patient-reported outcome measures. The specific research questions guiding this study design are listed in **Box 1**.

**BOX 1**. Study Research Questions.Feasibility Research Questions:RQ1a: How many referrals for prehabilitation will be received and what are the identified indications for prehabilitation?RQ1b: Does a surgeon’s bedside assessment of frailty (as indicated by referral and reason for referral) correspond with established frailty indices?RQ1c: What percentage of referred patients participate in prehabilitation?RQ1d: What are the demographic and medical characteristics of patients who are referred to for prehabilitation?RQ1e: What factors contribute to participants choosing either FBP or HBP?RQ1f: What is the ‘prehabilitation window’ for participants (i.e., time from treatment decision to surgery)?RQ1g: What is the adherence rate to the multimodal components defined by the prehabilitation protocols?RQ1h: Is prehabilitation safe within a clinical model of care (i.e., number and nature of adverse events)?RQ1i: What are the barriers and facilitators to prehabilitation?RQ1j: What are the various costs and potential cost savings associated prehabilitation?Exploratory Effectiveness Research Questions:RQ2a: What changes in clinically relevant outcomes do participants experience by the week prior to surgery and up to 90 days after surgery?RQ2b: Compared to usual care, what effect does prehabilitation have on peri- and postoperative outcomes (up to 90 days after surgery)?(RQ, Research Question)

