### Study Outcomes

Participant data to assess feasibility and derive estimates of effect are collected from the participants’ referrals, at the baseline assessment, within 1 week prior to surgery, and at 30 and 90 days postoperatively.

The total number of referrals and the rate at which they are received (per month) will be reported. To characterize the patients referred to the program, the following are collected from all referral forms (including usual care participants and those who decline research): referring surgical service; reason for referral; frailty level (*via* the Clinical Frailty Scale (3), embedded into the referral); cancer type; indicated surgery; referring healthcare practitioner type (*i.e.* physician, surgeon, clinic nurse, *etc.*), and participant demographics (age, sex, and general geographic location). The enrolment rate will be calculated as [# of enrolled participants]/[# of referred participants]. The frequency and reasons for declining participation in the study, declining prehabilitation (*i.e.*, usual care participants), and drop-out will be reported and compared using descriptive statistics of demographic and referral data.

Given the importance of scheduling and timing for prehabilitation relative to the date of surgery, several relevant time periods will be reported. The time from program referral to the date of surgery will be reported and is referred to as the ‘prehabilitation window’. We will also report the total preoperative period (time between consent for surgery and date of surgery) and prehabilitation duration (time from baseline assessment to surgery).

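### The Analytic Plan defines the retention rate as dropouts over enrolled, which is the attrition rate (minor correction)

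*Protocol article*

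**What the plan says.** The calculation rule is in the Analytic Plan: "Retention rates will be calculated as a total percentage of dropouts at the presurgical time point to the total participants enrolled", for FBP and HBP. The numerator is dropouts at the presurgical time point, the denominator is everyone enrolled in the two prehabilitation arms, and the result is called retention.

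Three other places bear on it:

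- Study Objectives: "The primary objective of this study is to assess the feasibility of delivering a multimodal surgical prehabilitation service to surgical oncology patients". Feasibility is therefore the main purpose of the pilot.
- The Methods part of the Abstract: "Feasibility data include program referral rates, enrolment and attrition, intervention adherence and safety". There the measure is named attrition.
- Study Outcomes, which commits to giving frequency and reasons for several kinds of non-participation, including "declining prehabilitation (*i.e.*, usual care participants), and drop-out will be reported". No time point is attached to that commitment.

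The Discussion adds that clinician frailty ratings will be set against adherence and study retention, without defining retention again.

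**The concern.** A retention rate should rise as more participants stay. The quantity in the Analytic Plan falls as more stay, because it counts those who left. An analyst who follows the sentence literally would tabulate attrition under the heading of retention.

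Two uses are exposed. First, a team planning a later trial or a clinical service from this pilot could read a low figure as poor retention when it means the opposite. Second, the Discussion plans to relate frailty to study retention. If that variable were coded in the direction of the Analytic Plan rule, an association in which frailer patients leave more often would appear as frailty going with higher retention.

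The Abstract says attrition and the Analytic Plan says retention for what is arithmetically the same quantity. A reader of the eventual report could not tell from the label alone which of the two had been printed.

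**Working it through.** **Is there a figure to reproduce?** No. The article states no retention figure, expected dropout or retention target. The check is therefore on the definition, with assumed dropout counts to show its effect.

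**Inputs**

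- Anticipated referrals: 150 over 12 months (Sample Size).
- Share expected to decline the intervention but allow use of their records: one third (Sample Size), so 150 × 1/3 = 50.
- Prehabilitation participants, FBP and HBP together: 150 − 50 = 100. This is an upper bound, since some referred patients may be ineligible or decline the research altogether.
- Presurgical dropouts, D: not given. Assumed range 5 to 50 out of 100.

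**Formulas**, with N enrolled and D presurgical dropouts:

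- Rule as written: D / N
- Retention: (N − D) / N = 1 − D / N

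**Results for N = 100**

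| Assumed dropouts D | Rule as written | Retention |
|---|---|---|
| 5 | 5% | 95% |
| 10 | 10% | 90% |
| 20 | 20% | 80% |
| 30 | 30% | 70% |
| 40 | 40% | 60% |
| 50 | 50% | 50% |

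The two are equal only when D / N = 1 − D / N, that is, at 50% dropout. Below that, the rule as written understates retention by 1 − 2D/N: 90 percentage points at 5 dropouts, 60 at 20, and 20 at 40.

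**Does another section override the rule?** No. The Abstract names attrition without a formula, Study Outcomes promises dropout frequency and reasons without a formula, and the Discussion mentions study retention without a definition. The Analytic Plan sentence is the only calculation rule for this rate.

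**Is information lost?** No. Numerator, denominator and time point are all stated, so retention is recovered by subtracting from 100%. The limits of a confidence interval convert the same way.

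**The case against.** The strongest defence is that this is a slip in a label. The Abstract promises attrition, and dropouts over enrolled is exactly that. Every component is stated, nothing has to be re-collected, and an analyst would probably notice before printing 20% as retention when 80% stayed. This stands as far as severity goes. It does not make the sentence correct, because the analysis section is where the calculation is fixed and no other section corrects it.

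It is also fair to say that retention is not a headline result. None of the ten feasibility questions in Box 1 names retention or dropout, and no progression criterion depends on it. A reader might infer from the primary feasibility objective that a primary endpoint is inverted or a go/no-go decision reversed. The article does not support that: attrition is one item in a list of feasibility data, and no threshold is attached to it.

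A second tempting reading is that stopping at the presurgical time point is itself an error, because data are collected "at the baseline assessment, within 1 week prior to surgery, and at 30 and 90 days postoperatively" and the plan models "changes in physical fitness, patient-reported outcomes from baseline to the 90-day time point using linear mixed effect models". The documents do not support this either. The intervention ends at surgery, so a presurgical rate is a coherent measure of retention in the programme. Dropout frequency (Study Outcomes) and reasons for dropout (both sections) are to be reported with no time limit, so postoperative loss need not go unreported. Complications, readmissions and length of stay come from the medical record, so a missed visit does not by itself lose them. Completeness of questionnaires at each visit is detail that an article can leave to the full protocol or the statistical analysis plan.

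**Conclusion.** The point holds in a limited form. The Analytic Plan gives the name retention to the attrition rate; applied literally, the reported figure is one minus retention. That follows from the wording alone and needs no assumption. Its size in this trial cannot be stated, because the article gives no expected dropout. The illustrative gap of 20 to 90 percentage points rests on assumed dropout of 5% to 40% among at most 100 participants.

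The consequence is a mislabelled descriptive feasibility figure and, if the same coding were carried over, a reversed sign when frailty is related to study retention. That carry-over is a risk, not something the article states, since the Discussion does not say how retention will be coded. No decision threshold, sample size or effect estimate is affected. The correction is minor but should be made before results are tabulated.

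**What to change.** Replace the sentence in the Analytic Plan in one of two ways:

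- Define the retention rate as (enrolled − presurgical dropouts) / enrolled for FBP and HBP, with a 95% confidence interval, in line with the emphasis on intervals stated in that section; or
- keep the calculation and call it the attrition rate, which matches the term in the Abstract.

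Whichever is chosen, use the same direction when frailty ratings are related to study retention, as the Discussion foresees.

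The cost is one sentence, with no new data and no change to the design. Reporting the same rate at 30 and 90 days, where assessments are already planned, would be a useful optional addition; it does not correct an error.
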